### Study design, setting, and participants

This MIND-STEP study is a superiority, single-blind, parallel-group randomized controlled trial designed in a 1:1 ratio to evaluate the effectiveness of a multicomponent exercise intervention among MCI older adults residing in a nursing home in China. The trial design and timeline are summarized in Fig. 1 and Table 1. Ethics approval was granted by the Medical Ethics Committee of Huzhou Third People’s Hospital and was registered (trial registration number ChiCTR2400088301). Participants will be randomly assigned in a 1:1 ratio to either an intervention group receiving 12 weeks of a multicomponent exercise program or a control group receiving usual care with no structured exercise intervention. Assessors responsible for performing the baseline (week 0), midline (week 6–7), endline (week 12–13), and follow-up assessments (weeks 24–25, corresponding to approximately 12–13 weeks post-intervention) will be blinded to allocation.

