### Intervention

#### Intervention group

Participants in the intervention group will receive a 12-week, group-based multicomponent exercise program to be delivered through in-person, face-to-face sessions. Each session will last 30 min and will be conducted twice per week. The multicomponent exercise intervention will consist of five structured components: a warm-up, aerobic training, resistance training, mind–body training, and a cool-down period, forming a complex, theory-informed approach tailored to the physical and cognitive needs of older adults. Participants will be guided by nurses in the nursing home to perform aerobic training, resistance training, and dual-task (mind–body) training throughout the 30-min session. A Rate of Perceived Exertion (RPE) of 5–6, corresponding to moderate intensity, will be recommended. Core aerobic exercises will include shoulder movements, hip abduction or extension, and thigh lifts. Resistance training will consist of functional movements such as squats and trunk twists. Mind–body training will incorporate coordinated activities such as seated marching combined with attention tasks and standing marching paired with inhibition tasks. All participants will be instructed to complete a brief warm-up at the beginning and a cool-down routine at the end of each session to promote safety and recovery.

The intervention will feature a group-based multicomponent exercise program and will be conceptually grounded in the integrated HAPA-TPB model. This theoretical framework was selected to address known facilitators and barriers to exercise engagement among older adults [23], as it incorporates both the motivational phase (e.g., intention formation) and the intenders phase (e.g., planning, execution, maintenance of behavior) and action phase, thereby providing a comprehensive framework for promoting sustainable health behavior change in later life. This integrated model combines the stage-based behavioral pathway of HAPA (preintenders, intenders, and actors) [24, 25] with key motivational determinants from TPB, including attitudes, subjective norms (operationalized as social support in this study), and perceived behavioral control [26]. Particular emphasis was placed on enhancing self-efficacy and peer-based social support as core mechanisms to strengthen adherence and sustain exercise behavior.

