#### Secondary outcome measures

Secondary outcomes include Quality of Life measured by the EuroQol-5D-5L (EQ-5D-5L), Activities of Daily Living (ADL), Pittsburgh Sleep Quality Index (PSQI) [29], intrinsic capacity, frailty, social support, and intervention cost and benefit, which have been validated among Chinese older adults. Intrinsic capacity will be evaluated in accordance with the WHO Integrated Care for Older People (ICOPE) guidelines [30], across the following domains: cognitive capacity assessed by MoCA-B, vitality assessed using Mini Nutritional Assessment–Short Form (MNA-SF), locomotion measured by Short Physical Performance Battery (SPPB), psychological status assessed using Patient Health Questionnaire (PHQ-9) [31], and sensory determined by self-reported vision and hearing questions. Frailty will be assessed using the frailty phenotype (FP) [32, 33], physical activity levels will be evaluated using the International Physical Activity Questionnaire–Short Form (IPAQ-SF), and social support will be assessed by the Lubben Social Network Scale (LSNS) [34].

Secondary outcomes will be assessed at baseline, 6 weeks, 12 weeks, and 24 weeks post-randomization. Secondary endpoints will be defined as the between-group differences in change from baseline at each post-randomization timepoint. Results will be reported as adjusted mean differences or risk differences with corresponding 95% confidence intervals, as appropriate to the outcome type. All secondary analyses will follow the intention-to-treat principle.

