#### Process evaluation

A comprehensive process evaluation will be conducted to assess the quality of intervention implementation and its potential impact on study outcomes. This evaluation will address the following dimensions: Eligibility and recruitment will be tracked using data on the proportion of eligible participants, recruitment and retention rates, and reasons for drop-off. Intervention acceptability will be evaluated through supervisory documents, adherence records and satisfaction surveys [35]. Adherence will be measured based on the number of dropouts and session frequency across groups. Participants will be classified as having dropped out if they meet any of the following criteria: average training frequency of ≤ 2 times per week over 3 weeks; average frequency of ≤ 1 time per week for two consecutive weeks; or no sessions completed within a 1-week period. Temporary absences of 1–2 weeks due to medical treatment or personal reasons will be exempt if participants resume full participation thereafter. All dropouts will be encouraged to complete follow-up assessments.

Outcome acceptability will be assessed by calculating the completion rates of outcome questionnaires at baseline, 6 weeks, and 12 weeks. Adverse events, including falls, fractures, muscle strains, cardiovascular events, and new or exacerbated musculoskeletal, cardiovascular, or metabolic conditions, will be monitored throughout the study. Participants in the intervention group will be asked about any adverse events following each session. All reported events will be documented and the responsible authorities will be notified promptly, and relevant free examinations and management strategies will be provided within the nursing home or referred to the appropriate medical institution. Participants experiencing minor adverse events may continue with the study if the participants’ condition does not worsen and if adequate rest and treatment do not interfere with ongoing participation.

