### Data collection and management

The trial will be coordinated by the Huzhou Third Municipal Hospital, the Affiliated Hospital of Huzhou University, which is responsible for overall study management and coordination across study sites. Data management will be conducted by trained research staff under the supervision of the principal investigator at Peking University. An independent data monitoring committee and endpoint adjudication committee will not be established due to the low-risk nature of the behavioral intervention; however, study progress, protocol adherence, and data quality will be regularly reviewed by the core research team. Any protocol deviations or adverse events will be documented and discussed in regular team meetings. Data quality will be ensured through double-entry and regular audits. Personal data will be kept confidential, and no personal information will be reported.

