**Fig. 2 Fig2:**
[figure not shown]
Trial profile

Baseline characteristics are presented in Table 3. A total of 156 participants were randomized to either the exercise intervention group (*n* = 78) or the control group (*n* = 78). The mean age of the total sample was 69.19 years (SD = 8.97), with a higher proportion of female participants (*n* = 108, 69.23%) than male participants (*n* = 48, 30.77%). The two groups were generally well-balanced at baseline, with no statistically significant differences observed in age, gender, marital status, educational attainment, Hukou status, occupation and monthly income.

**Table 3 Tab3:** Baseline characteristics of participants

**Variable**	**Intervention group** (*N* = 78)	**Control group** (*N* = 78)	*χ*^2^/*F*	*P* value
**Age (year)**	68.63(8.61)	69.76(9.35)	0.610	0.434
**Sex**			0.120	0.729
Male	23 (29.49)	25 (32.05)		
Female	55 (70.51)	53 (67.95)		
**Marital status**			0.027	0.869
Married or partnered	48 (61.54)	49 (62.82)		
Other	30 (38.46)	29 (37.18)		
**Educational attainment**			0.026	0.872
Primary school and below	42 (53.85)	43 (55.13)		
High school and above	36 (46.15)	35 (44.87)		
**Hukou**			0.103	0.748
Urban	37 (47.44)	35 (44.87)		
Rural	41 (52.56)	43 (55.13)		
**Occupation**			2.136	0.711
Government or institutional staff	7 (8.97)	4 (5.13)		
Skilled professional/technical personnel	6 (7.69)	6 (7.69)		
Agricultural workers	10 (12.82)	14 (17.95)		
Others	47 (60.26)	43 (55.13)		
Unemployed or not currently working	8 (10.26)	11 (14.10)		
**Household income per month**			0.045	0.978
Low income (tertile 1)	28 (35.90)	28 (35.90)		
Middle income (tertile 2)	33 (42.31)	34 (43.59)		
High income (tertile 3)	17 (21.79)	16 (20.51)		

Continuous variables are reported as mean ± SD and analyzed using ANOVA; categorical variables are reported as frequency (%) and analyzed using chi-square tests

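### Adverse-event questioning after each session is specified for the intervention arm alone, so by-arm counts of minor events would not be comparable

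*Protocol article*

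**What the plan says.** The Process evaluation section lists falls, fractures, muscle strains, cardiovascular events and new or worsened musculoskeletal, cardiovascular or metabolic conditions, and says that these "will be monitored throughout the study". That statement is not restricted by arm, but it gives no method and no frequency. The one method described follows directly: "Participants in the intervention group will be asked about any adverse events following each session".

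The Intervention group section fixes how often that happens: "Participants in the intervention group will receive a 12-week, group-based multicomponent exercise program", and "Each session will last 30 min and will be conducted twice per week". The comparator is "a control group receiving usual care with no structured exercise intervention" (Study design, setting, and participants), so controls have no session after which they could be asked.

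Both arms share the outcome visits: "Secondary outcomes will be assessed at baseline, 6 weeks, 12 weeks, and 24 weeks post-randomization". No adverse-event question is mentioned at those visits. Under Data collection and management, "Any protocol deviations or adverse events will be documented and discussed in regular team meetings"; the Trial monitoring section adds monthly review and reporting of serious events to the ethics committee. These steps deal with events already known to the team. They do not say how a control participant's event becomes known.

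**The concern.** Most of the listed events are not specific to exercise. Residents with a mean SPPB of about 7 and poor distance vision in over 80% of each arm (Table 4) can fall or strain a muscle in either group. For minor events, the number recorded depends partly on how often people are asked.

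If one arm is questioned twice a week and the other is observed only in routine care, a by-arm table mixes the effect of exercise with the effect of asking. The distortion has a known direction: apparent harm from exercise is inflated. A real reduction in minor falls could be masked, and a real increase would look larger than it is. The trial means to inform wider use of exercise in long-term care, so readers are likely to look for exactly this comparison. Analysis cannot recover control-arm events that nobody asked about.

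**Working it through.** The document gives no adverse-event rate, detection probability or safety power, so there is no figure of the plan to reproduce. What can be checked is the number of enquiries and how unequal detection would carry through to the counts.

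**Planned enquiries per participant**
- Intervention: 12 weeks × 2 sessions = 24.
- Control: 0 stated.
- If both arms were also asked at the three follow-up visits (not stated), the contrast would be 24 + 3 = 27 against 3.

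**Apparent ratio with no true difference.** Let *c* be passive capture as a fraction of active capture. Assume *c* = 0.3 to 0.6; nothing in the document supports or contradicts this range.
- Weeks 0–12, with session questioning in one arm: ratio = 1/*c*. This gives 1/0.6 = 1.7 and 1/0.3 = 3.3.
- Weeks 0–24: sessions stop at week 12, so capture is *c* in both arms for the second half. With events spread evenly, ratio = (1 + *c*)/(2*c*). This gives 1.6/1.2 = 1.3 and 1.3/0.6 = 2.2.

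**What this could do to a test at this trial's size.** "A total of 156 participants were randomized to either the exercise intervention group" or control, 78 per arm. Assume a true risk of 20% in both arms and 90% detection with session questioning, so the exercise arm shows 0.20 × 0.90 = 18%. The last column is the chance of a nominally significant excess in the exercise arm (two proportions, two-sided 5%), which would be 2.5% in that direction with equal detection.

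| Detection in controls (assumed) | Apparent control risk | Apparent risk ratio | Chance of a false excess |
|---|---|---|---|
| 75% | 15% | 1.2 | about 7% |
| 50% | 10% | 1.8 | about 30% |
| 25% | 5% | 3.6 | about 73% |

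This table applies one detection level to the whole comparison, so it describes the session period and not the full 24 weeks.

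**By type of event.** Both arms live in homes that provide personal, toileting and safety care (Control group section). Fractures and serious cardiovascular events are likely to surface there without questioning, so *c* should be near 1 and the ratio near 1. The figures above concern strains, soreness and minor falls.

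**The case against.** The strongest objection is that no between-arm comparison of adverse events is planned. They sit under process evaluation, are not listed as a primary or secondary outcome, and do not appear in the analysis of outcomes. Asking exercisers after a session is a sensible safety check on the intervention. This stands: the point applies only if events are reported or compared by arm.

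Second, a reader might infer that controls are never asked. The document does not support that. The general monitoring statement covers the whole study, and the full protocol, which is not shown, may describe a control-arm procedure. The accurate contrast is 24 enquiries against none stated. Still, the article is not merely silent on ascertainment: it states a method and ties it to one arm.

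Third, a reader might apply the 1.7–3.3 ratio to the whole trial, or to every listed event. Neither is supported. It rests on assumed capture, covers weeks 0–12 only, and has little bearing on fractures or serious cardiovascular events. Nor would the unequal questioning hide a harmful effect; it would exaggerate one.

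Fourth, the obvious remedies have weaknesses. Nursing-home nurses guide the sessions, and reported events are managed in the home or referred, so session-elicited events can enter the facility records. Answers that mention sessions can also unblind an assessor. Both stand, and the fix has to allow for them.

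**Conclusion.** The point holds as a conditional one. As written, adverse-event ascertainment is more intensive in the exercise arm during weeks 0–12, and by-arm counts of minor self-reported events from that process would not be comparable. The bias runs against the intervention.

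Its size is unknown. The ratios of 1.7–3.3 (weeks 0–12) and about 1.3–2.2 (24 weeks) rest on the assumed 30–60% passive capture and, for the longer period, on events spread evenly over time. The primary MoCA-B analysis is not affected. The document does not support a conclusion that a planned safety analysis is biased, because none is announced. It does support settling the source of the events before any by-arm table is produced.

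**What to change.** - State how adverse events in controls are found.
- Put the same structured adverse-event questions to both arms at the week 6, 12 and 24 visits, covering the time since the last visit. Ask them after the MoCA-B and the other outcomes are scored, so that answers cannot unblind the assessor beforehand.
- Base any between-arm comparison only on sources common to both arms: those visits and routine facility incident records. Flag and exclude record entries that arose only from session questioning.
- List session-elicited events descriptively, for the intervention arm alone.
- If the visits are already past, restrict the comparison to serious or medically attended events in facility records and state the unequal ascertainment as a limitation. This may well be the case: recruitment was expected to end by March 2025, and 25 weeks later is about September 2025. Reported events lead to free examinations, so the flagging of session-prompted entries matters here too.

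The cost is a few extra questions at existing visits, or a short statement in the analysis plan before database lock. The drawbacks are reliance on recall over 6 to 12 weeks in people with MCI, and some remaining risk that an answer at one visit unblinds the assessor for later ones.

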### Sample size estimation

The sample size was calculated using PASS 2021 software (version 21.0.3). A two-sample independent *t*-test based on effect size was used for estimation, with cognitive function as the primary outcome. Previous studies have reported effect sizes of exercise interventions on cognitive improvement ranging from 0.54 to 2.85 [36–39]. To ensure a conservative estimation, an effect size of 0.54 for cognitive improvement was selected. With a two-sided significance level of *α* = 0.05 and statistical power of 85% (1 − *β* = 0.85), a minimum of 126 participants (63 per group) was required. To account for an anticipated 20% attrition rate, the planned recruitment target was set at 160 participants (80 per group). Due to unavoidable circumstances, such as relocation or death during the recruitment period, 156 participants were ultimately enrolled, which remained sufficient to meet the predefined statistical power requirements.

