### Randomization and blinding

Participants were randomly assigned to either the intervention or control group in a 1:1 ratio using a computer-generated randomization sequence. The allocation sequence was generated in advance by an independent researcher who is not involved in participant recruitment, outcome assessment, or data analysis. Allocation concealment was implemented using a centrally maintained randomization list held by a designated study supervisor independent of recruitment and assessment procedures. The allocation list was not accessible to recruiters or outcome assessors. After eligibility confirmation and completion of baseline assessments, participants were assigned sequentially according to the predefined randomization list in the order of enrollment. Group allocation was disclosed only after baseline assessments were completed.

Due to the nature of the behavioral intervention, participants and intervention providers cannot be blinded to group allocation. However, outcome assessors will remain blinded to group allocation throughout the study to minimize assessment and analytical bias. Outcome assessors will not have access to the randomization list and will be instructed to avoid any discussions with participants regarding their assigned groups. Participants will also be reminded not to disclose their group allocation during assessments. Unblinding will be permitted only in cases of medical emergencies where knowledge of the participant’s allocated intervention is essential for patient safety. The procedure for unblinding involves contacting the principal investigator or designated study physician, who will access the allocation information from the secure trial database and document the reason for unblinding.

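### The statement that 156 participants keep the predefined 85% power is not supported: it falls marginally short at the planned attrition and makes no allowance for group delivery of the exercise

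*Protocol article*

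**What the plan says.** Under Sample size estimation, the protocol article names the method: "A two-sample independent *t*-test based on effect size was used for estimation, with cognitive function as the primary outcome". It takes the lowest of the effect sizes it cites, which run from 0.54 to 2.85: "an effect size of 0.54 for cognitive improvement was selected". With a two-sided 5% level the result is "statistical power of 85% (1 − *β* = 0.85), a minimum of 126 participants (63 per group) was required". For an expected 20% attrition the target was set at 160. Recruitment ended at 156, 78 per arm, and the section closes with the claim that "156 participants were ultimately enrolled, which remained sufficient to meet the predefined statistical power requirements". It shows no recalculation at 156 and mentions no design effect, ICC or exercise-group size.

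Allocation is individual: "Participants were randomly assigned to either the intervention or control group in a 1:1 ratio using a computer-generated randomization sequence". Treatment in the active arm is not: "The intervention will feature a group-based multicomponent exercise program". The Intervention group section names peer-based social support as a core mechanism. Table 2 adds a consistent instructor, peer role models and reinforced group norms.

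**The concern.** Two things do not fit the sufficiency statement. First, the section's own inputs (126 evaluable, 20% loss) imply more than 156 randomised. Second, the calculation counts every participant as an independent observation, while those in the intervention arm share sessions, an instructor and deliberate peer influence. Such sharing tends to make outcomes within an exercise group alike. The treated arm then carries less information than its head count suggests.

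The stake is interpretation. If the trial is null, readers will take the published statement to mean that an effect of 0.54 SD had an 85% chance of being detected. If group correlation is present and attrition is as planned, the chance under the stated method is lower, by an amount the article does not let the reader judge.

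**Working it through.** **Inputs from the article:** standardised effect d = 0.54; two-sided α = 0.05; power 85%; 1:1 allocation; 126 evaluable; attrition 20%; 156 randomised (78 + 78).

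**Assumed, not in the documents:** exercise-group size m and ICC.

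**Step 1. Reproduce the plan's figure.** Two-sample t-test, noncentral t, noncentrality d × √(n/2) with n per arm:
- n = 62: power 84.7%
- n = 63: power 85.25%

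The minimum is 63 per arm, 126 in total. The stated figure reproduces exactly.

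**Step 2. Attrition.**
- Needed: 126 / 0.80 = 157.5, so 158 randomised. The target of 160 covered this (160 × 0.80 = 128).
- Achieved: 156 × 0.80 = 124.8, or 62.4 per arm.
- Power at 62.4 per arm: 84.9%; rounded down to 62 per arm: 84.7%.
- Break-even attrition: 1 − 126/156 = 19.2%, that is 30 people lost.
- With no attrition (78 per arm): 91.8%.

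**Step 3. Group delivery in one arm only (partially nested).** The design effect DE = 1 + (m − 1) × ICC applies to the intervention arm alone:

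SE = √(DE/62.4 + 1/62.4), power = Φ(0.54/SE − 1.96)

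Worked case, m = 10 and ICC 0.05: DE = 1 + 9 × 0.05 = 1.45; SE = √(2.45/62.4) = 0.198; 0.54/0.198 = 2.725; Φ(2.725 − 1.96) = Φ(0.765) = 77.8%.

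| m | ICC | DE | Power at 62.4 per arm |
|---|---|---|---|
| any | 0 | 1.00 | 85.5% |
| 6 | 0.01 | 1.05 | 84.6% |
| 10 | 0.01 | 1.09 | 83.9% |
| 10 | 0.02 | 1.18 | 82.4% |
| 10 | 0.05 | 1.45 | 77.8% |
| 10 | 0.10 | 1.90 | 70.7% |
| 15 | 0.10 | 2.40 | 63.8% |

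The ICC 0 row is the same formula without clustering. It gives 85.5% where the exact t-test gives 84.9%, so the normal approximation is about half a point generous and the losses should be read against 85.5%.

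**Step 4. Same formula with no attrition.** With 78 per arm, m = 10 and ICC 0.05: SE = √(2.45/78) = 0.177, power about 86%. The shortfall therefore depends on attrition being near its planned value as well as on the ICC.

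**The case against.** The case on the other side is substantial.

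- **The attrition gap is trivial.** It is one or two people and at most 0.3 power points, and the result still rounds to 85%. The 20% is a round planning figure, and dropouts are encouraged to complete follow-up assessments. The mixed model uses all time points, so a participant missing week 12 can still contribute. This stands: a reader who inferred from the attrition arithmetic that the claim is materially wrong would be overreading it.
- **Neither group size nor ICC is given.** With an ICC near zero the loss disappears. This stands as to size, but not as to direction: no positive ICC raises power, and the unclustered figure has no margin at the planned attrition.
- **The calculation credits nothing for efficiency.** The planned analysis adjusts for covariates and uses repeated measures, and 0.54 is the bottom of the cited range. This stands in part. Net power of the planned model cannot be determined, particularly as the article does not say whether 0.54 is in SD units of the week-12 score or of the change. But the section does not rest its claim on these gains.
- **The unseen statistical analysis plan may contain a group-level random effect.** The article lists only fixed effects, so one cannot infer that the analysis ignores clustering. Such a term would protect the standard error; it would not restore the published power.

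A reader might also infer that real power is about 64%. The documents do not support that: the figure pairs the largest assumed group with the largest assumed ICC. Nor do the several nursing homes by themselves add to the case, because individual randomisation should largely balance differences between homes across arms.

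**Conclusion.** The point holds in a limited form. The figure of 126 is correct. At exactly 20% attrition, 156 randomised falls 1 to 2 short of it, with 84.7–84.9% power under independence, which is marginal. The substantive defect is that the sufficiency claim rests on an independence assumption that does not fit group delivery in the intervention arm. At the planned attrition, any positive within-group correlation takes the power of the stated calculation below 85%.

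The size of that loss rests on assumed values: about 84% to 78% for 10 per group and ICC 0.01 to 0.05, and about 85% to 64% over the wider span of 6 to 15 per group and ICC 0.01 to 0.10. All of these are before any gain from the baseline-adjusted repeated-measures model. They are illustrations and should not be read as the trial's actual power.

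**What to change.** In Sample size estimation, replace the sentence on sufficiency with three statements:

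1. With 156 randomised and 20% attrition, about 125 participants are evaluable, marginally below 126, giving about 85% power for d = 0.54 if participants are independent.
2. A partially nested sensitivity range, computed from the exercise-group sizes actually formed and a stated ICC range, with the ICC values labelled as assumptions.
3. Whether 0.54 is in SD units of the week-12 MoCA-B score or of its change from baseline. If the sponsor wishes to credit the repeated-measures model, the assumed correlation should be stated as well.

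No extra enrolment or design change is asked for. The cost is a short recalculation and a slightly less favourable stated power.
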